### Group composition

The 72 participants will be allocated to the control and experimental groups as follows (Figs 1 and 2):

**Fig 2 pone.0349031.g002:**
[figure not shown]
Flowchart of study.

Control group – PBM simulation (n = 36 participants): All participants in this group will undergo the conventional IUD placement procedure, as described above. They will receive sham PBM and be treated the same as the experimental group. The researcher in charge of the PBM application will simulate irradiation by positioning the device in the exact location as in the experimental group, but the equipment will be switched off. To prevent the participants from identifying the group to which they belong, the activation sound of the device (beep) will be pre-recorded and played during the sham application.Experimental group – active PBM (n = 36 participants): All participants will undergo the same IUD placement procedure. For irradiation, an LED panel from Sportlux^®^ (Brazil, SP) (Fig 3) will be used. The equipment description, dosimetric parameters, and number of PBM applications are detailed in Table 1.

**Table 1 pone.0349031.t001:** Dosimetric Parameters Used for Preventive PBM.

Technical Parameters	Values
Light source	LED **_**
Application technique	Contact
Wavelength	132 LEDs at 660 nm/ 132 LEDs at 850 nm
Spectral band	20 nm
Beam area on target	0.5 cm²
Irradiation time	20 min
Average power per LED	8 mW
Irradiance	16 mW/cm²
Application time	10 minutes
Energy per LED	4.8 J
Radiant exposure	9.6 J/cm²
Light emission angle	120°

nm- nanometro, W- Watt, J- Joule.

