Given the lack of effective pharmacological interventions, alternative approaches have been explored. Paravertebral blockade between T10 and S4 has shown promise for analgesia during labor [2,5,9], while transcutaneous electrical nerve stimulation (TENS) has been effective at controlling pelvic pain [10,11]. Photobiomodulation (PBM) has demonstrated analgesic effects for lower back pain [12,13] and labor pain [9], suggesting the potential to reduce discomfort during IUD placement [14]. As the Brazilian Ministry of Health does not currently recommend analgesic measures for IUD placement, further studies are needed to assess the effectiveness of PBM at improving patient comfort and increasing adherence to this contraceptive method, ultimately benefiting public health [4]. Our experimental hypothesis is that the use of PBM can reduce pain perception during the placement of the T 380 copper IUD for contraception.

Therefore, the aim of this study is to propose a protocol for the assessment of whether preventive photobiomodulation (PBM) alters pain perception during the placement of the T 380 copper intrauterine device (IUD) for contraception in women without comorbidities.

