**Fig 1 pone.0349031.g001:**
[figure not shown]
Template illustrating recommended content for schedule of enrollment, interventions, and assessments.

The study protocol (original language S2 File; in English S3 File) received approval from the Research Ethics Committee of the Mandaqui Hospital Complex in São Paulo, Brazil (7.367.867). The original document (S4 File) and a translation (S5 File) were presented Any unforeseen events or modifications during the study will be reported to the ethics committee and disclosed in future publications. After the main investigator provides a verbal and written explanation of the study, individuals who agree to participate will sign an informed consent form. Participants who wish to receive the study results will provide their email addresses and the full article will be shared upon publication. The participants will be involved in the development of the study design and the execution of the trial but not involved in the data analysis or reporting.

Treatment will be performed at the Mandaqui Hospital Complex in the northern region of São Paulo, Brazil. The main investigator is a gynecologist with more than 10 years of experience and will perform the procedures. According to the ClinicalTrials.gov record (NCT06984796) (S6 File), the study is currently listed as “Not yet recruiting”, with an anticipated starting date of March 30, 2026, and a primary completion date of May 30, 2027. The study was registered in ClinicalTrials.gov (NCT 06984796) and is in accordance with the SPIRIT 2025 Guidelines Checklist Statement.

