### Allocation (Sequence generation, allocation concealment mechanism, implementation)

A random sequence generator available online (https://www.sealedenvelope.com/) will be used to select the block randomization option with two treatments at a 1:1 ratio, resulting in equal numbers of patients in each group (n = 36 per group). As the total sample size is 72 patients, 12 blocks of six patients each will be established. Opaque envelopes will be sequentially numbered (1–72) and will contain the randomized group allocation. These envelopes will be sealed and stored securely until the IUD is placed. Only the designated researcher responsible for treatment will be aware of the assigned intervention. After opening, the envelope will be resealed and stored with the patient’s medical record, remaining concealed until the final statistical analysis. An individual not directly involved in the study will generate the random sequence and prepare the envelopes.

All participants will undergo the same IUD placement protocol performed by the same healthcare provider, as described in the “IUD Placement Protocol” section. Immediately after placement, the researcher in charge of applying PBM will retrieve and open an envelope, maintain the order of the remaining envelopes, and administer the assigned treatment (active or sham PBM). Only this researcher will be aware of the allocation.

The main investigator will oversee data storage (digital platforms) and organization. The statistician will be responsible for data analysis and will remain blinded to the interventions. The envelopes will also store participant records (patient history questionnaire, demographic data, risk factors, and statement of informed consent) and will be securely archived.

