**Fig 3 pone.0349031.g003:**
[figure not shown]
Sportlux^®^ LED panel used for preventive irradiation during IUD placement. Legend: Source: Created by the authors. Figure A: Panel switched off. Figure B: Panel switched on.

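### Table 1 prints two undefined treatment times, 20 min and 10 min, and the stated light dose fits only 10 min per LED per site

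*Protocol article*

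**What the plan says.** The experimental arm is specified by Table 1 (Dosimetric Parameters) in the Group composition section of the protocol article. The table has two time rows: "Irradiation time 20 min" and, further down, an application time of 10 minutes. It also gives a beam area of 0.5 cm², an average power of 8 mW per LED, an irradiance of 16 mW/cm², an energy of 4.8 J per LED and a radiant exposure of 9.6 J/cm². The light source is described as "132 LEDs at 660 nm/ 132 LEDs at 850 nm".

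The text introducing the table says that the "number of PBM applications are detailed in Table 1", but the table as shown has no row with that number. Of the control arm it says: "They will receive sham PBM and be treated the same as the experimental group". No separate sham duration is given.

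The full protocol is cited as a supplement ("The study protocol (original language S2 File; in English S3 File") and is not shown.

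**The concern.** Power is fixed by the device, so time is the part of the dose that the operator controls. Two different times for what reads as one procedure leave the session length open. The row labelled as irradiation time is the natural one to set a timer by, and it is the row that does not fit the stated dose. An operator who followed it at a single site would give twice the energy that the article reports. A later reader could not tell which exposure had been tested. The sham session inherits the same uncertainty, because it is to mirror the active one.

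**Working it through.** All inputs are from Table 1: power P = 8 mW = 0.008 W per LED; beam area A = 0.5 cm²; irradiance I = 16 mW/cm² = 0.016 W/cm²; energy E = 4.8 J per LED; radiant exposure H = 9.6 J/cm²; times 10 min (600 s) and 20 min (1200 s).

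**1. Do the dose rows agree with each other?**
- I = P / A = 8 / 0.5 = 16 mW/cm², as printed.
- H = E / A = 4.8 / 0.5 = 9.6 J/cm², as printed.

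**2. What time do they imply?**
- t = E / P = 4.8 / 0.008 = 600 s = 10 min.
- t = H / I = 9.6 / 0.016 = 600 s = 10 min.

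**3. What would 20 min at one site deliver?**
- E = 0.008 × 1200 = 9.6 J per LED.
- H = 0.016 × 1200 = 19.2 J/cm².
- Both are twice the printed values.

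**4. What would keep the stated dose over 20 min at one site?**
- P = 4.8 / 1200 = 0.004 W = 4 mW.
- I = 9.6 / 1200 = 0.008 W/cm² = 8 mW/cm².
- Both are half the printed values.

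**5. How do the possible readings differ?** Panel energy is not stated in the article. The last column assumes that each of the 132 + 132 = 264 LEDs emits 8 mW when lit, so the whole panel emits 264 × 0.008 = 2.112 W and one wavelength set 132 × 0.008 = 1.056 W.

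| Reading | Per LED per site | Panel energy per session |
|---|---|---|
| 10 min, one site | 4.8 J; 9.6 J/cm² | 2.112 × 600 = 1267.2 J |
| 20 min in total, wavelength sets in turn, 10 min each | 4.8 J; 9.6 J/cm² | 1.056 × 600 × 2 = 1267.2 J |
| 20 min in total, two sites, 10 min each | 4.8 J; 9.6 J/cm² | 2.112 × 600 × 2 = 2534.4 J |
| 20 min continuous, one site | 9.6 J; 19.2 J/cm² | 2.112 × 1200 = 2534.4 J |

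The first three readings agree with the printed dose; the fourth does not.

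**6. Overlap with the assessments (conditional).** The Allocation section puts treatment after placement: "Immediately after placement, the researcher in charge of applying PBM will retrieve and open an envelope". If the session starts at placement, 10 min ends 5 min before the 15-minute assessments (15 − 10 = 5), and 20 min ends 5 min after them (20 − 15 = 5). Either length is still running at the 5-minute pain score. The Introduction suggests treatment beforehand, with "preventive photobiomodulation (PBM) alters pain perception during the placement" as the question, and the Fig 3 legend speaks of an "LED panel used for preventive irradiation during IUD placement". If treatment is finished before placement begins, no pain score taken during or after placement falls within the session. The order of treatment and placement is a separate question and is not settled here.

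**The case against.** The strongest reply is that no sum in the table is wrong. Application time may mean the time per application and irradiation time the total, and the text does speak of a number of applications, which could be more than one. Two 10-minute sites, or the red and infrared sets in turn, would satisfy every printed row. On that view the table is ambiguous, not contradictory, and simply changing 20 to 10 could delete correct information. The full protocol and the figures are not shown and may supply the count. One designated researcher gives all treatments, which makes variation in dose between participants less likely. The sham is already tied to the active procedure.

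Much of this stands. The dose arithmetic is sound for 10 min, the benign readings are possible, and the correction has to depend on which reading is meant. The absent application count carries little weight, since a supplement may give it, and the panel energies rest on an assumption. The timing point is conditional, and even 10 min would not clear the 5-minute score.

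It does not remove the defect. The table prints two times without saying what either one measures, and nothing shown reconciles them. A count in a supplement would not correct a published table that can be read as twice its own stated dose. A single operator makes delivery consistent but does not decide which time is used.

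**Conclusion.** The point holds. Table 1 as written does not fix a unique session length. The printed dose corresponds exactly to 10 min of on-time per LED per site. Read as continuous irradiation at one site, the 20 min row contradicts that dose by a factor of 2 (9.6 against 4.8 J; 19.2 against 9.6 J/cm²). That factor is the upper end of a range from 1 to 2. Under either benign reading of 20 min as a total, the dose per LED per site is as stated.

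The per-LED result rests only on figures printed in the table. The consequence is limited: the intended dose can be recovered, the arms are still handled alike, and sample size and significance level are untouched. It should nevertheless be fixed before treatment begins, because it sets the exposure delivered and reported for the only experimental intervention.

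**What to change.** Before the first participant, decide which reading is meant and make Table 1 say so.

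- If there is one 10-minute application, replace 20 min with 10 min, or merge the two time rows into one.
- If 20 min is a total, label it as such, say whether it covers two sites or the two wavelength sets in turn, and give the number of applications and sites.
- Under either choice, energy must equal power × on-time, and radiant exposure must equal irradiance × on-time, per LED per site. The 4.8 J and 9.6 J/cm² then stay as printed.
- State explicitly that the sham session has the same duration, and check that the supplementary protocol gives the same times.

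The cost is one corrected table row, plus one label or count if 20 min is a total. The article describes the trial as not yet recruiting, so on its own account no participant would be affected. Sample size and analysis do not change.

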**Fig 3 pone.0349031.g003:**
[figure not shown]
Sportlux^®^ LED panel used for preventive irradiation during IUD placement. Legend: Source: Created by the authors. Figure A: Panel switched off. Figure B: Panel switched on.

### Outcome variables

#### Primary outcome.

Pain – Assessed using the Visual Analog Scale (VAS) at baseline, during the IUD placement phases (Pozzi, hysterometry, and IUD placement), 5 and 15 minutes after placement as well as 24 and 48 hours after the procedure.

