## Materials and methods

A single-center, randomized, double-blind, controlled clinical trial with two parallel groups, designed as a superiority trial, will be conducted following the schedule of enrollment (Fig 1) and SPIRIT Statement (https://www.spirit-statement.org/) (S1 File).

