### Sample size calculation

The total sample size will be 72 participants. This number was calculated to provide an 80% power (α = 0.05) with an effect size of 0.14. The number of patients per group was determined using a sample size calculation with G*Power 3.1.9.7. The sample was calculated for two groups, and 8 measurements will be performed: at baseline, during the IUD insertion phases (Pozzi, hysterometry, and IUD placement), at 5 and 15 minutes after placement, and at 24 and 48 hours after the procedure.

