Cervical clamping: Gently clamp the anterior lip of the cervix using Pozzi forceps to stabilize it during placement.Hysterometry: Slowly and carefully insert the hysterometer to determine uterine depth and angulation, minimizing the risk of uterine perforation.Placement of IUD in the uterine cavity

*Secondary outcome – Description of pain – Free Narrative*: Immediately after IUD placement, the patients will be asked to describe their experience with the procedure. The responses will be recorded verbatim to enable qualitative analysis.

*Secondary outcome – Quantity of analgesics (amount taken by the patient will be recorded at 24 and 48 h after the T 380 copper IUD placement*: Analgesic (paracetamol) consumption will be assessed as proposed by Bauer et al. (2013; [18]). At the beginning of the study, each participant will receive a blister pack of paracetamol, which is a pure analgesic [19]. The blister pack must be kept until the end of the study, and the analgesic will be used only for pain. At the end of the study, the number of remaining tablets will be quantified as an additional measure of pain. The analgesic will be paracetamol 500 mg to be taken only when necessary at a dosage of one tablet every six hours. The participants will be asked to record in writing the number of tablets taken, along with the date and time of consumption. A monitoring procedure will be implemented to ensure adherence: the participants will be required to bring their blister pack to follow-up visits for verification. Medication use will be tracked from baseline through 48 hours post-placement.

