### Statistical analysis

Statistical analysis will be performed using the Statistical Package for the Social Sciences (SPSS) version 24.0 or equivalent software package. The significance level will be set at 5% (p < 0.05) for all tests. Data normality will be determined using the Shapiro-Wilk test. Continuous variables will be reported as either the mean and standard deviation or the median and interquartile range, depending on the distribution of the data. Categorical variables will be expressed as absolute and relative frequencies. For comparisons between the experimental group (active PBM) and control group (sham PBM), the Mann-Whitney test will be used for continuous variables with non-normal distribution. When the expected minimum value is less than 5, categorical variables will be compared using either the chi-square test or Fisher’s exact test. The analysis of pain-related variables (intensity measured by the Visual Analog Scale [VAS]) at different time points (baseline, during placement, 5 and 15 minutes, and 24 hours after the procedure) will be conducted using the Friedman test. As the primary outcome will be measured repeatedly over time, the analysis will account for the within-subject correlation inherent to this repeated-measures design.

For the measures of anxiety (GAD-7), quality of life (WHOQOL-100), and satisfaction with the procedure, the Mann-Whitney test will be used to compare groups across assessment time points. The use of post-procedural analgesics will be compared between groups using repeated-measures analysis of variance (ANOVA). No interim analyses or stopping guidelines are planned due to the short duration of the trial and low risk.

Missing data will be assessed for frequency and pattern. In the event of missing values, the analyses will be performed using the available data, and the extent of missingness will be reported. If necessary, appropriate statistical methods will be applied depending on the nature and proportion of the missing data.

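### Primary VAS pain is spread over eight readings with no primary time point, no between-arm test fixed for it and no multiplicity rule, so the type I error of the superiority claim is not controlled

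*Protocol article*

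**What the plan says.** All of this is in the protocol article.

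- **Materials and methods** describes the trial as "designed as a superiority trial".
- **Primary outcome** is a single line: VAS pain at baseline and "during the IUD placement phases (Pozzi, hysterometry, and IUD placement), 5 and 15 minutes after placement as well as 24 and 48 hours". That is eight readings, one of them baseline. No reading is singled out, and no mean, maximum or area under the curve is defined.
- **Sample size calculation** uses the same eight: "The sample was calculated for two groups, and 8 measurements will be performed". It adds: "This number was calculated to provide an 80% power (α = 0.05) with an effect size of 0.14".
- **Statistical analysis** states: "The significance level will be set at 5% (p < 0.05) for all tests". For VAS over time it names the Friedman test, in a list that omits 48 h and merges the three insertion steps. For comparing arms it names Mann-Whitney, in general terms, for non-normal continuous variables. It adds that the primary analysis will allow for within-subject correlation, but names no model that does so between arms. Repeated-measures ANOVA appears only for analgesic use.
- **Allocation** has the envelope opened and PBM given after placement. The Introduction calls PBM preventive and puts the hypothesis on pain during placement.
- **Secondary outcomes** provides paracetamol for 48 hours: "the analgesic will be used only for pain".

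**The concern.** A superiority claim needs one comparison of the arms, or a rule for combining several. Neither is fixed here. Friedman's test asks whether pain differs between times in the same women. It will reject whenever insertion hurts more than baseline, whether or not PBM works. The between-arm test named for a non-normal continuous variable, Mann-Whitney, takes one value per woman. With no summary measure defined, its natural use is reading by reading, each at 5%.

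Two things are at stake. The false-positive rate of the superiority claim is not controlled. There is also no rule for the conclusion if the readings disagree. They measure different things: pain from instruments, pain minutes later, and pain at 24 and 48 h, when women may have taken paracetamol.

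**Working it through.** **Inputs from the article.** 5% per test (Statistical analysis); 36 per arm (Allocation). Readings: eight listed; seven after baseline; six if 48 h is left out as in Statistical analysis (insertion steps counted separately); four after placement.

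**Assumptions.** Two-sided tests, because sidedness is not stated. Within-woman correlation ρ from 0 to 0.9, because no value is given. The effect size 0.14 is read as Cohen's f, because its type is not named.

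**1. The plan's own figure, N = 72.** Repeated-measures ANOVA with k = 2 groups and m = 8 readings, under sphericity:
- Group-by-time interaction: λ = f²Nm/(1−ρ), with (k−1)(m−1) and (N−k)(m−1) degrees of freedom. N for 80% power is 94 at ρ = 0, 76 at 0.20, 70 at 0.25 and 48 at 0.5.
- Between groups: λ = f²Nm/(1+(m−1)ρ), with 1 and N−2 degrees of freedom. N is 54 at ρ = 0, 88 at 0.1 and 228 at 0.5.

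The interaction test gives 72 for an unstated ρ between 0.20 and 0.25. The figure can therefore be neither confirmed nor called wrong. It does suggest that one repeated-measures test was in mind, yet Statistical analysis names no such between-arm test of VAS.

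**2. False-positive risk if each reading is tested.** For K independent tests, either direction: 1 − 0.95^K. Favouring PBM only: 1 − 0.975^K.
- K = 7: 1 − 0.95⁷ = 0.302; 1 − 0.975⁷ = 0.162.
- K = 4: 1 − 0.95⁴ = 0.185; 1 − 0.975⁴ = 0.096.

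For correlated readings, equicorrelated normal test statistics were simulated (400,000 runs). Chance of at least one false positive:

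| Readings tested | ρ = 0 | 0.5 | 0.7 | 0.9 |
|---|---|---|---|---|
| 7, either direction | 30.2% | 23.0% | 17.9% | 11.4% |
| 7, favouring PBM | 16.2% | 11.5% | 8.9% | 5.7% |
| 6, either direction | 26.5% | 20.8% | 16.5% | 10.7% |
| 4, either direction | 18.5% | 15.5% | 13.0% | 9.3% |
| 4, favouring PBM | 9.6% | 7.8% | 6.5% | 4.7% |

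The nominal values are 5% in either direction and 2.5% favouring PBM. Simulated Mann-Whitney tests with 36 per arm (20,000 runs) agree for seven readings: 22.9% at ρ = 0.5 and 18.2% at 0.7. With correlation decaying over successive readings (AR(1), 0.7 to 0.9) the figure is 22.7% to 15.1%.

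**3. After a correction.** One pre-specified between-arm test restores 5% (2.5% favouring PBM). If the readings stayed co-equal, Bonferroni levels would be 0.05/7 = 0.0071 or 0.05/4 = 0.0125.

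**4. Effect on power at N = 72.**
- Single reading, two-sample t test: 80% power needs a standardized difference d of about 0.67. If 0.14 is f, then d = 2 × 0.14 = 0.28, for which power is about 22% and about 202 per arm would be needed.
- One arm effect over the three insertion steps: λ = 0.14² × 72 × 3/(1 + 2ρ). At ρ = 0.5, λ = 2.12 and power is about 30%; at ρ = 0, λ = 4.23 and power is about 53%.

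**The case against.** The strongest reply is that the article nowhere says VAS will be tested between arms at each reading, or that one significant reading counts as success. It assigns Mann-Whitney across time points only to anxiety, quality of life and satisfaction. It promises to allow for within-subject correlation, and it sized the trial on two groups and eight measurements. A single omnibus between-arm test would hold 5%. This stands in part: the inflation is conditional. It does not remove the point, because no such test is named and the VAS test that is named does not compare arms.

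A reader might also infer more than the documents support:
- **That the risk of falsely claiming PBM superior is 18–30%.** That range counts differences in either direction. The part favouring PBM is about 9–16%.
- **That the range is a property of the plan.** It depends on an assumed correlation and on how many readings follow treatment.
- **That the hypothesis singles out the final placement step.** The Introduction speaks of pain during placement, and Secondary outcomes counts three moments within it.
- **That a baseline difference could count as success.** Listing baseline reads as part of the measurement schedule.

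Could an unseen analysis plan settle this? Order and adjustment often sit there. The definition of the primary endpoint belongs in the protocol, and this one sets all readings level under a blanket 5% rule.

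**Conclusion.** The point holds in conditional form. The primary outcome has no primary time point or summary, no between-arm repeated-measures test of VAS is named, and 5% applies to every test without a multiplicity rule. The inflation arises only if the seven post-baseline readings are compared separately and any significant one is accepted. Its size then rests on two-sided testing and an assumed correlation: over ρ from 0.7 to 0 it is roughly four to six times the nominal 5%, and still more than double at 0.9. It is smaller if treatment follows placement, since only four readings could then respond to it. The correction is needed before recruitment, because at present nothing defines what would confirm superiority.

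**What to change.** 1. Reconcile the statements on when PBM is given relative to placement. Which readings can show an effect depends on this.
2. Name one primary between-arm test at two-sided 5% that matches the hypothesis and the sample size calculation. An example, provided the reconciled order puts these readings after irradiation, is a single pre-specified arm effect from a repeated-measures mixed model over the Pozzi, hysterometry and IUD placement readings, with baseline VAS as covariate. If a single reading is preferred, restate the power for it.
3. Make the remaining readings secondary, tested in a fixed order or with Holm's adjustment. Use one list of readings throughout, including 48 h.
4. Report the 24 h and 48 h VAS alongside paracetamol taken. Tablet counts and times are already to be recorded.

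**Cost.** Protocol and registry wording; no new data collection. The other readings lose confirmatory status. The sample size justification must be restated for the chosen test, giving the type of effect size and the assumed correlation. That step is substantive: if 0.14 is Cohen's f, 72 women may be too few for an average arm effect or a single reading.
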